### **4. Interventions**

The intervention scheme of this trial will be based on expert consensus and result of

previous pilot study(23). There will be 1 full-time acupuncturists per center (4 acupuncturists in total in 4 centers) responsible for operation of acupuncture and sham acupuncture. In general, acupuncturists will be assigned to the same participants throughout the 3-cycle treatment schedule, except for vacation conflicts and staff turnover. All acupuncture treatments were delivered by acupuncturists who were registered with Ministry of Health of the People's Republic of China with more than 20 years of clinical experience. Sterile disposable steel acupuncture needle (size: 0.25 mm×25 mm for head points, 0.3 mm×40 mm for limb and abdomen points, Hwato Needles, made in Suzhou, China) will be used in this trial. It took 9 cycles in total for a patient to complete the trial, 3 cycle's baseline assessment, 3 cycle' treatment, and 3 cycle' follow up.

#### **4.1 Treatment of the acupuncture group**

In the acupuncture group, participants will be given true acupuncture plus placebo naproxen (2 tablets each time, once per day, will start three days before each predicted onset of the menstruation and continue during the end of their menstrual cycle for 3 cycles). In the event that menstruation begins later than predicted, no adjustment to the treatment will be made. If the MRM occurs earlier than predicted, participants will be asked to begin taking placebo naproxen immediately and one day earlier in the next cycle in an attempt to provide prophylactic coverage. The timing of treatment will be based on information collected (a headache diary) during the baseline phase and will not account for variability in menstruation and migraine onset during the treatment phase. The placebo naproxen will be identical in taste, smell and appearance as true naproxen sustained release tablets.

Acupuncture will consist of preventive treatment (two sessions each week) and premenstrual conditioning treatment (at least three sessions during 10 days before the predicted onset of each menstruation), deliver for 3 cycles. Each session will last for 30 minutes. The acupuncture points for preventive treatment will include both standard and additional points. The standard points are GV20 (Baihui), GV24 (Shenting), GB13 (Benshen), GB8 (Shuaigu), TE20 (Jiaosun), and GB20 (Fengchi). Additional points will be chosen individually depending on the syndrome differentiation of meridians in the headache region: TE5 (Waiguan) and GB34

(Yanglingquan) for Shaoyang headache; LI4 (Hegu) and ST44 (Neiting) for Yangming headache; BL60 (Kunlun) and SI3 (Houxi) for Taiyang headache; LR3 (Taichong) and GB40 (QiuXu) for Jueyin headache; PC6 (Neiguan) for nausea and vomiting, and LR3 (Taichong) for dysphoria and susceptibility to rage. For premenstrual conditioning, each participant will have standard acupuncture points, KI12 (Dahe), CV3 (Zhongji) and ST29 (Guilai). All of the selected acupuncture points will be determined based on our previous research (16). After sterilizing the skin, the needle will be inserted 10 to 15mm in depth and manipulated by rotation methods to produce a characteristic sensation known as de qi (feeling of needle sensation refers to tenseness around the needle felt by the practitioner and numbness, distension, soreness, and heaviness around the point felt by the patient) at each point. Ten to twelve sterile disposable steel needles in each session will be used for acupuncture.

#### **4.2 Treatment of medication group**

In the medication group, participants will be given naproxen sustained release tablets (Diao Group Chengdu Pharmaceutical LTD, Chengdu, China) plus sham acupuncture. Naproxen sustained release tablets will be taken with a peri-menstrual dosing strategy (250mg/tablet, 2 tablets each time, once per day), which will start three days before each predicted onset of the menstruation and continue until the end of their menstrual cycle for 3 cycles. In the event that menstruation begins later than predicted, no adjustment to the treatment will be made. If the MRM occurs earlier than predicted, participants will be asked to begin taking naproxen immediately and one day earlier in the next cycle in an attempt to provide prophylactic coverage. The timing of treatment will be based on information collected (a headache diary) during the baseline phase and will not account for variability in menstruation and migraine onset during the treatment phase.

The method of applying blunt needles on effective acupuncture points will be not used in this trial as control for following reason: patients in China are very familiar with the sensations caused by acupuncture and therefore they may easily identify the blunt needles.

To make the needling stimulation consistent, the same type, size, and number of needles will be used for both groups. In order to avoid possible therapeutic effects of sham acupuncture,

the non-effective acupoints are chosen by the following three rules: (1) Acupuncture points that are defined as unrelated to headache or menstruation based on a vast amount of Chinese medicine reference books (26 ancient Chinese books of acupuncture, three Chinese acupuncture textbooks and >100 acupuncture research literatures); (2) 15 acupuncture points in the vicinity of elbow and knee joints are selected while the acupuncture points on the head, hands, feet, and trunk are excluded; (3) To mimic the nature of selecting points based on syndrome differentiation, the 15 sham points in the vicinity of elbow and knee joints are further randomly assigned to 3 subgroups: B, C, D. Each subgroup will have two points on the arms and three points on the legs. The participants in the medication group will be further randomly assigned into one of these three subgroups via central randomization system. Participants will be treated individually to avoid communication on the treatments they received.

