#### **2.4.2 Subjects**

##### **2.4.2.1 Eligibility criteria**

Women will be included in the study if they met the following criteria. (1) Diagnosis of MRM(24): MRM without aura (code A1.1.2), in which migraine without aura always occurs on days  $1 \pm 2$  of menstruation in at least two out of three menstrual cycles, and at other times due to different triggering factors or for no apparent specific reason (International Classification of Headache Disorders - second edition [ICHD-II]); (2) Regular menstrual cycle (25-35 days); (3) could predict within three days both the onset of menstruation and perimenstrual migraine attacks; (4) Repeated migraine attacks, frequency of nonmenstrual migraine is more than once

a month; (5) Written informed consent.

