**Figure 3. The schedule of enrollment, interventions, and assessments**

## **2.4.4 Outcomes Measurements**

### **2.4.4.1 Primary Outcome**

The primary outcome will be the change from baseline in average number of migraine days per perimenstrual period over cycles 1-3, assessed using headache diary data(14).

Calculation methods:

Average number of migraine days per perimenstrual period over cycles 1-3 is calculated as the cycle average, equals the total of migraine days during perimenstrual period over cycle 1, cycle 2 and cycle 3 divided by 3.

The frequency and severity of migraine will be based on data from headache diary recorded by participants on baseline (Cycle- -3 to Cycle-0), treatment phase (Cycle-1 to Cycle-3) and follow-up phase (Cycle-4 to Cycle-6). In the diaries, the participants recorded on diary cards with details of their migraine attacks, including the time of headache attack and cease, intensity, frequency, location (the forehead, top, temporal, and back of the head), cause of the headache, concomitant symptoms, and acute pain medications (if any) for each migraine attack. Additionally, participants were required to record information of their menstruation and the dates of receiving acupuncture treatments in their headache diaries. If acute pain medications were taken, participants were required to document the name, dosage, and time of taking the medicine, time of pain relief, and side effects of acute pain medication. In each center, data of headache diaries will be checked by two full-time research assistants first, and then entered into e-headache diary database by two independent data entry clerks. The audited data of e-headache diary will be finally carried forward into effectiveness data by statisticians.

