#### **6.3.5 Safety Analyses**

##### **Adverse events**

All adverse events and serious adverse events will be listed. Adverse events include the acupuncture-related adverse events and medication-related adverse events. Chi-square test or Fisher's exact test will be used to compare the incidence of adverse events between the acupuncture group and medication groups.

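### Protocol 4.1 and 4.2 name the wrong stop event for the tablets: the end of the menstrual cycle, where the end of menstruation is most likely meant

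*Supplement*

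**What the plan says.** Protocol 4.2 describes naproxen, two 250 mg tablets once a day, as "taken with a peri-menstrual dosing strategy". Each course begins three days before the predicted onset of menstruation and is to "continue until the end of their menstrual cycle for 3 cycles". Protocol 4.1 gives the matching placebo the same start and dose, but there the course is to "continue during the end of their menstrual cycle for 3 cycles".

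Three further rules govern timing in both arms:

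- Late menses: "In the event that menstruation begins later than predicted, no adjustment to the treatment will be made".
- Early migraine: tablets start at once, and the next course starts a day sooner.
- Schedule: "The timing of treatment will be based on information collected (a headache diary) during the baseline phase".

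The eligibility criteria (2.4.2.1) show what the protocol means by a cycle: "Regular menstrual cycle (25-35 days". SAP 6.3.5 tests the proportion of women who reached 80% or more of their planned acupuncture or medication. For safety, a chi-square or Fisher's exact test "will be used to compare the incidence of adverse events between the acupuncture group and medication groups".

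**The concern.** The stop rule is an operative dosing instruction for four centers, and it names an event that does not fit the regimen around it. The protocol elsewhere keeps *menstrual cycle* for the whole interval and *menstruation* for the bleed. A course that begins three days before menses and runs to the end of the cycle which that menses opens is still running when the next course is due.

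Four things depend on the number of tablet days:

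- the comparator's exposure to naproxen, in a protocol whose Background (2.2) warns of medication-overuse headache;
- the adverse-event comparison, because Protocol 3 attributes events to medication by their link to tablet intake within 24 hours;
- the secondary outcomes outside the perimenstrual period over cycles 1-3, because continuous dosing would put active drug on those days in one arm only;
- the medication-compliance percentage, whose denominator is the planned number of tablet days.

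**Working it through.** **Does any literal reading fit?**

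1. *To the end of the cycle that the menses opens.* Dosing is continuous. This conflicts with the perimenstrual label. It also leaves nothing to restart before each predicted onset and no gap in which the next course could begin a day sooner.
2. *To the end of the cycle in progress when tablets start.* Tablets stop as menses begins, after three days. Most of the treatment window cited in Protocol 2.2 (two days before to three days after onset) is then uncovered.
3. *To the end of menstruation.* This fits the label, the repeated start and the early-migraine rule. Item (1)a of Protocol 11 also shows that the authors once used *menstrual cycle* loosely for what they now call the perimenstrual period.

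**How far apart are the readings?** The plan states no number of tablet days, so there is no figure to reproduce.

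Inputs:

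- lead-in of 3 days, 3 courses, 2 x 250 mg = 0.5 g per day (Protocol 4.2);
- cycle length L = 25 to 35 days (Protocol 2.4.2.1);
- bleeding length m = 3 to 7 days (assumed; not in the documents).

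| Stop event | Formula | Tablet days | Naproxen | Days to reach 80% |
|---|---|---|---|---|
| End of the cycle opened by the menses (literal, continuous) | 3 + 3L | 78 to 108 | 39 to 54 g | 63 to 87 |
| End of menstruation (most likely intent) | 3 x (3 + m) | 18 to 30 | 9 to 15 g | 15 to 24 |
| End of the cycle in progress at the start | 3 x 3 | 9 | 4.5 g | 8 |

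The last column is 0.8 x tablet days, rounded up: 62.4, 86.4, 14.4, 24.0 and 7.2 become 63, 87, 15, 24 and 8.

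Ratio of continuous to menstruation reading:

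- smallest (L = 25, m = 7): 78/30 = 2.6;
- largest (L = 35, m = 3): 108/18 = 6.0;
- L = 28, m = 5: 87/24 = 3.6.

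A woman who follows the menstruation rule perfectly would score between 18/108 = 16.7% and 30/78 = 38.5% against a continuous denominator, and so would fail the 80% criterion.

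**Does it reach the primary outcome?** The primary outcome counts migraine days in the perimenstrual period. The continuous and menstruation readings both put tablets on the days around menses, and both arms carry the same end point. The SAP does not tie the compliance percentage to the primary analysis. Only the nine-day reading would remove naproxen from menses itself, and nothing in the text supports that reading.

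**The case against.** The best reply is that nobody reading the whole paragraph would dose continuously. The perimenstrual label, the restart before each menses and the early-migraine rule all point the same way, and Protocol 6 requires training in delivering the interventions. The several-fold figures then describe a regimen that the context rules out, and they need a bleeding length the documents do not give. This stands as a limit on weight: the figures show what the sentence literally orders, not what probably happened. It does not make the sentence right.

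A second reply is that the intent may be the end of the perimenstrual window rather than of menstruation, since the change log replaced the loose term with *perimenstrual period* and the cited window ends three days after onset. That is possible. It would give 3 + 3 = 6 days per course (18 in all), or 3 + 1 + 3 = 7 (21 in all) if the onset day is counted separately. Both lie within the 18-30 range, so the scale is unchanged, but it is a reason to ask the sponsor.

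Third, the documents predict the onset of menses, never its end. A stop day taken from the baseline schedule is consistent with the timing rules but is not stated. That stands.

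A reader might infer more than the text supports:

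- *That women took naproxen daily for three months.* Nothing shows that any site did so.
- *That the arms had different stop rules.* 4.1 and 4.2 differ by one preposition, which reads as a language slip; the end point is the same and the double-dummy balance holds.
- *That the primary comparison is biased.* The check above does not support this.
- *That no usable tablet instruction exists anywhere.* The consent pages were removed from the text reviewed and may be clearer.

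**Conclusion.** The stop event in Protocol 4.1 and 4.2 is wrong as written and should be corrected. Confidence is high that *menstrual cycle* is the wrong term. That *menstruation* is meant is the most likely reading but not certain.

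The consequences are limited to exposure, the adverse-event comparison, the outcomes outside the perimenstrual period, and the denominator of the 80% medication-compliance measure. The 2.6- to 6.0-fold gap illustrates the literal rule under an assumed 3-7 day bleed; it does not estimate any actual difference in dosing. The firmest practical consequence is the compliance measure: planned medication cannot be counted consistently until the stop event is fixed, and the same tablet count could pass or fail. The matter is worth correcting because the sentence is an operative instruction and the correction is cheap, not because it threatens the primary result.

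**What to change.** Put one identical sentence in Protocol 4.1 and 4.2: tablets start three days before each predicted onset of menstruation and continue until the end of menstruation, for 3 cycles.

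Ask the sponsor to confirm that the stop day follows the schedule predicted from the baseline diary. That agrees with the existing rules, which ignore variation during treatment, but it means tablets may stop before bleeding does when menses is late. The sponsor should accept that explicitly or choose the actual end of bleeding.

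In SAP 6.3.5, define planned medication as the resulting tablet days, plus any day added by the early-migraine rule, and use that as the denominator for the 80% criterion.

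The cost is one sentence in two sections and one line in the SAP. Compliance is already scheduled in each treatment cycle, and for the diary "participants were required to record information of their menstruation". The text does not say whether that includes the last day of bleeding; if it does not, the diary needs one more field. No visit, test or sample-size change follows.

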#### **4.3 Permitted and prohibited concomitant treatments**

Throughout the whole trial, participants will be discouraged from any prophylactic medications of MRM, such as other non-steroidal anti-inflammatory drugs (NSAIDs), triptans, estrogen, magnesium, dihydroergotamine (DHE), methysergide and vitamin E. For any treatment already used, related information should be recorded in case report form.

### **5. Informed Consent**

## **6. Quality Control**

To guarantee the quality of the study, the trial protocol will be reviewed and may be revised by expert acupuncturists, neurologists, and statisticians several times. A central randomization system will be adopted to avoid selection bias. Strict eligible criteria will be pre-set to restrict the research population. Blinded effect assessment and blinded statistics will be designed to

guarantee the objectivity of the data. All research staffs, especially the research assistants, acupuncturists and data entry clerks, will be required to attend a series of training on how to use the central randomization system and data entry system, how to fill the case report form and headache diary, how to manipulate interventions correctly, and how to assess the outcomes, etc. A double-entry method will be used in this trial. The data of therapeutic evaluating will be calculated by the statisticians. A three-level inspection plan will be designed for quality inspecting.

## **7. Data Management**

### **7.1 The Raw Data Management and Archiving**

We will use Remote Data Capture (RDC) system to perform data entry. The research assistants will fill out all the electrical CRF through RDC system. Researchers will inspect the eCRF, and signed electrically for the eCRF going into effect. The eCRF and the trace of eCRF revising will be left in the Oracle database.

### **7.2 Data Entry and Storage**

#### **7.2.1 Database Building and Testing, Data Entry Interface**

The eCRF will be noted through CDISC CDASH standard, and the data entry interface will be generated through the Oracle Clinical software. The data entry interface should be in accordance with the paper version CRF as far as possible. The inputted data will be stored in the Oracle database. After preliminarily setting up the database, the entry clerks will input some analog data according to the CRF to test the database. The testing contains: (1) the agreement of the data entry interface and the paper version CRF; (2) the agreement of the exported data from the database and the analog data. After the testing, data administrators should revise the database and make a testing report. Then they electrically signed on the approval page of the database to indicate that the testing is completed. The electrical files of the analog CRF, Noted CRF, screenshot of the data entry interface, database testing report, and the approval page of the database should be saved. If the database updates during the trial, the electrical files

mentioned above are also need to be updated.

### **7.2.2 Data Entry and Inspection**

The research assistants take charge of the data entry for our trial. Before the entry, all the research assistants will accept the related training according to the data entry handbook. Researchers will inspect the database, and then sign electrically to let the data go in to effect.

### **7.3 Data Verification and Problems Solving**

Researchers will verify the data through Data Verification Plan (DVP) approved by the data administrator and the statisticians. Data queries will be inputted to a data query database, and form the Data Clarification Form (DCF). After being inspected, the DCF will then be handed back to the original center, and the researchers of the center should answer the queries. Any revision of the database will be recorded through the RDC software.

### **7.4 Medical Coding**

A data administrator who has the medicine background will take charge of the medical coding. The contents of the coding are the clinical history, adverse events, and combined medication. The clinical history and adverse events will be coded through MedDRA dictionary (Version 13.0), and the combined medication will be coded via WHO DD dictionary (Version 2007.03). The lead researchers will verify the coded e-files.

### **7.5 Data Blinding Review and Data Management Report**

When the data checking is finished, a data auditing and blinding review meeting will be hold. On the meeting, the data administrators, statisticians, researchers, clinical inspectors, and other related members would have a discussion on the following items according to the data management report and the data lists:

- Distribution of the participants;
- Protocol deviation;
- Possible outlier;

- Baseline data review;
- Outcomes review;
- AEs review;
- Classifying plan of the statistical analysis population;
- Statistical analysis plan.

Participants will be classified to their suitable statistical analysis sets according to the definition in the protocol. No patient can be excluded from the analysis, unless getting the permission of the meeting participants. All the meeting participants should sign the data locking consent, and the data auditing resolution.

## **7.6 Database Locking**

The database will be locked if it fulfills all the aspects as followed: All the queries have been solved, and the database has been updated; No query has been found through the data inspection; The medical coding has been completed; The plan of the participants' classification has been approved; The final draft of the SAP has been made, and approved by the project leader.

The statisticians and the data administrators will sign the data locking form, and then the database will be locked. The locked database will be sent to the statisticians for further statistical analysis through the data format of SAS.

## **8. Statistical consideration**

The following is an overview of the statistical considerations. Details of the pre-specified statistical analyses can be found in the Statistical Analysis Plan (SAP).

### **8.1 Statistical Analysis**

The primary study hypothesis is that acupuncture is different from medication in decreasing migraine days for women with MRM. The primary outcome is the change from baseline in average number of migraine days per perimenstrual period over cycles 1-3, assessed using headache diary data. The primary analysis will be intention-to-treat with the last observation carried forward (LOCF) method. Migraine days during perimenstrual period will be

summarized in each treatment group and compared using mixed-effect model.

The following secondary outcomes will be analyzed using the mixed-effect model, *t* test, Wilcoxon rank-sum test, Chi-square test or Fisher's exact test, as appropriate and the intent-to-treat principal:

1. Change from baseline in average number of migraine days per perimenstrual period over cycles 4-6
2. Change from baseline in average number of migraine days per outside perimenstrual period over cycles 1-3 and cycles 4-6
3. Change from baseline in mean migraine hours during perimenstrual period over cycles 1-3 and cycles 4-6
4. Change from baseline in mean migraine hours during outside perimenstrual period over cycles 1-3 and cycles 4-6
5. Change from baseline in mean pain VAS during perimenstrual period over cycles 1-3 and cycles 4-6
6. Change from baseline in mean pain VAS during outside perimenstrual period over cycles 1-3 and cycles 4-6
7. Proportion of participants with at least 50% reduction from baseline in number of migraine days during cycles 1-3 and cycles 4-6
8. Proportion of participants using acute pain medication during cycles 1-3 and cycles 4-6
9. Success rate of blinding at cycle 1.5 and cycle 3

A two-side test with  $p < 0.05$  will be considered significant for all analyses.

